## Abstract

**Background:**

Emergence agitation (EA) is a common postoperative issue in children that causes self-injury, increases stress on healthcare team members, and even leads to postoperative maladaptive behavioral changes in children. Clear answers regarding a ‘gold standard’ for prevention of EA are not available. Pain is regarded as an important causative factor of EA, and ultrasound-guided lumbar plexus block is a safe and efficient anesthetic method that can provide satisfactory pain relief in pediatric hip surgery. The purpose of our study is to determine whether ultrasound-guided lumbar plexus block can reduce the incidence of EA in children undergoing hip surgery.

**Methods/design:**

We designed a prospective, randomized, controlled, blinded trial to determine the effect of ultrasound-guided lumbar plexus block on EA. A total of 100 American Society of Anesthesiologists class I–II children (1–6 years old) scheduled for elective hip surgery will be recruited for this study. Participants will be randomized at a 1:1 ratio to receive either ultrasound-guided lumbar plexus block or fentanyl after the induction of general anesthesia. The primary outcome is the incidence of EA 30 min after emergence from anesthesia using the Pediatric Anesthesia Emergence Delirium (PAED) score. The secondary outcomes are the severity and duration of EA 30 min after emergence from anesthesia using the PAED score, postoperative pain evaluated by the Children’s Hospital of Eastern Ontario Pain Scale, and the incidence of postoperative adverse events. Randomization will be conducted using a computer-generated randomization schedule. Outcome assessors and data collectors will be blinded to the group allocations. Assessments will be performed before surgery, intraoperatively, and postoperatively at every time point.

**Discussion:**

Our hypothesis in this trial is that ultrasound-guided lumbar plexus block can decrease the incidence of EA in children undergoing elective hip surgery. This trial will provide clinical answers to verify our hypothesis. If our hypothesis is confirmed, the results could provide a safe method to prevent EA.

**Trial registration:**

Chinese Clinical Trial Registry, ChiCTR-INR-17011525. Registered on 30 May 2017.

**Electronic supplementary material:**

The online version of this article (10.1186/s13063-018-3140-3) contains supplementary material, which is available to authorized users.

## Background

Emergence agitation (EA) is a common phenomenon in the early postanesthetic period in children aged 3–9 years, which was first described by Eckenhoff et al. [1] in the early 1960s. The incidence of EA ranges from 10 to 80% [2, 3]. Although EA is short-lived, as it lasts an average of 30 min and is self-limiting [4], it may cause children to be prone to self-injury, interfere with a child’s recovery, increase healthcare costs, present a challenge to pediatric anesthesiologists, and decrease parents’ satisfaction with anesthesia [5–10]. Furthermore, EA is associated with postoperative maladaptive behavioral changes [11] and was recently considered a ‘vital sign’ [12]. Methods to prevent and treat EA have gained increased interest in pediatric anesthesia, but no gold standard method is currently available.

A variety of studies have investigated numerous contributors to EA, but the exact etiology of EA remains unclear. Inhalational agents with low blood solubility and pain are regarded as two significant predisposing factors of EA. The frequency of EA in children has increased due to the growing use of sevoflurane in general anesthesia, and nerve block administration can decrease the amount of sevoflurane used [13]. Pain plays an important role in EA [14–16], and adequate pain control can reduce the incidence of EA [6]. Numerous studies have reported that lumbar plexus block can provide superior analgesia effects that last 14.5 h [17]. Ultrasound technology has increased in popularity in pediatrics for lumbar plexus block because ultrasound guidance can provide direct visualization of the lumbar plexus to ensure both the safety and efficacy of lumbar plexus block [18–20]. However, controversies concerning the effect of nerve block on EA exist [13, 21–23], and trials studying lumbar plexus block on EA have not been performed.

We designed this prospective, randomized, and blinded study in children undergoing elective hip surgery and hypothesized that ultrasound-guided lumbar plexus block may decrease the incidence of EA in children undergoing elective hip surgery. This trial will provide clinical answers to verify our hypothesis and recommendations for clinical practice.

## Methods

### Ethical aspects and informed consent

This trial was approved by the Ethics Committee of the Shanghai Sixth People’s Hospital affiliated to Shanghai Jiao Tong University. This study was registered at the Chinese Clinical Trial Registry (http://www.chictr.org.cn/) under number ChiCTR-INR-17011525 on May 30, 2017. All parents of eligible participants will be informed of the objective of trial, the randomization procedure, the workflow, and the potential risks and benefits of each intervention. We will obtain approval and written informed consent from parents of children scheduled for elective hip surgery.

### Study design

This study is designed as a single-center, prospective, randomized, controlled, blinded trial. The schedule of enrollment and assessments is presented in the Standard Protocol Items: Recommendations for Interventional Trials (SPIRIT) figure (Fig. 1 and Additional file 1).

**Fig. 1 Fig1:**
[figure not shown]
Standard Protocol Items: Recommendations for Interventional Trials schedule of enrollment, intervention, and assessments. CHEOPS Children’s Hospital of Eastern Ontario Pain Scale, PAED Pediatric Anesthesia Emergence Delirium

### Objectives

#### Primary objective

The aim of our trial is to determine whether ultrasound-guided lumbar plexus block will reduce the incidence of EA in children undergoing elective hip surgery.

#### Secondary objectives

The secondary objectives are as follows:to compare the severity and duration of EA between the ultrasound-guided lumbar block group and the control group;to compare postoperative pain between the two groups; andto compare the occurrence of postoperative complications between the two groups.

### Study setting

This study will be conducted in Shanghai Sixth People’s Hospital affiliated to Shanghai Jiao Tong University, where approximately 200 pediatric hip surgeries are performed each year.

### Study population

Children scheduled for elective hip surgery will be recruited according to the following inclusion and exclusion criteria.

### Inclusion criteria

Prior to enrollment, patients must comply with all of the following:Undergoing elective hip surgery.Age 1–6 years.American Society of Anesthesiologists (ASA) class I–II.Informed parental consent provided.Suitable for general anesthesia and lumbar plexus block.

### Exclusion criteria

Patients are excluded if presenting any of the following:Lack of consent.Contraindication for lumbar plexus block.Developmental delay.Neurological or psychiatric disease.Local infection at the needle entry point.Coagulopathy.Nerve injury.Allergy to anesthetics and study medications.

### Outcomes and measurements

#### Primary outcome

The primary outcome of this study is the incidence of EA 30 min after emergence from anesthesia, which will be evaluated using the Pediatric Anesthesia Emergence Delirium (PAED) scale.

#### Secondary outcomes

The secondary outcomes are as follows:The severity and duration of EA 30 min after emergence from anesthesia evaluated using the PAED scale.The intensity of postoperative pain evaluated using the Children’s Hospital of Eastern Ontario Pain Scale (CHEOPS) scale.The incidence of postoperative adverse events.

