### Ultrasound-guided lumbar plexus block group

Patients assigned to ultrasound-guided lumbar plexus block group will be placed in a lateral decubitus position with the hips flexed and the operative site facing upward. The S-Nerve™ Ultrasound System (Sonosite Inc., Bothell, WA, USA) will be used for the ultrasound scan. After aseptic preparation of the lumbar region and transducer, nerve block will be performed with a linear array (6–13 MHz) transducer using the longitudinal approach. All blocks will be performed by the same anesthesiologist experienced and qualified in ultrasound-guided lumbar plexus block. All investigators are trained at the beginning of the study to ensure a standardized intervention and minimize the potential bias.

A line will be drawn to connect the iliac crests and identify the fourth lumbar spine. The ultrasound probe will be placed lateral and parallel to the long axis of the spine at the level of L3–L4. The entry site will be 1.5–2 cm lateral to the midline along the intercristal line. The needle will be advanced cautiously perpendicular to the skin with ultrasound guidance until the tip of the needle reaches 1–1.5 cm below the space between the transverse processes of L3 and L4. To avoid a possible vascular puncture, repeated negative aspirations will be performed during all needle advancements. The lumbar transverse processes exhibit a hyperechoic reflection and acoustic shadows on ultrasound scans, which can produce a ‘trident sign’. The roots of the lumbar plexus are located in the posterior portion of the psoas muscle 1–1.5 cm below the space between the transverse processes. When the needle is in place, 1 ml/kg of 0.2% ropivacaine (Naropin 10 mg/ml; AstraZeneca, Wilmington, DE, USA) will be injected. The maximum dose of local anesthetic is limited to 20 ml, and the injection speed of ropivacaine will be approximately 1 ml/s.

The adequacy of the ultrasound-guided lumbar plexus block will be defined by the visualization of the needle tip in the correct position; the spread of local anesthetic around the lumbar plexus nerves; increases in the heart rate, blood pressure, and respiratory rate of less than 15% in response to the skin incision; and increases in the intraoperative heart rate, blood pressure, and respiratory rate of less than 25%.

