The operation will be performed at least 15 min after the nerve block. During the operation, anesthesia will be maintained with 60% nitrous oxide, 40% oxygen, and 2% end-tidal sevoflurane. If the increases in heart rate, noninvasive blood pressure, and respiratory rate are greater than 15% from the baseline the values during the operation, the concentration of sevoflurane will be increased by 0.5%. Conversely, if the reductions in heart rate, noninvasive blood pressure, and respiratory rate are greater than 15% of the baseline values during the operation, the concentration of sevoflurane will be reduced by 0.5% [23]. If additional fentanyl is required when the heart rate, blood pressure, and respiratory rate increase by greater than 25% intraoperatively, the patient will be recorded as a failure or an inadequate lumbar plexus block and also be followed up. Immediate complications will be recorded and treated.

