### Control group

Children assigned to the control group will receive a bolus injection of 1 μg/kg fentanyl intravenously before skin incision. During the operation, anesthesia will be maintained with 60% nitrous oxide, 40% oxygen, and 2% end-tidal sevoflurane. If the increases in the heart rate, noninvasive blood pressure, and respiratory rate are greater than 15% of the baseline values during the operation, then the concentration of sevoflurane will be increased by 0.5%. Conversely, if the heart rate, noninvasive blood pressure, and respiratory rate are reduced by greater than 15% of the baseline values during the operation, then the concentration of sevoflurane will be decreased by 0.5%. Furthermore, if the heart rate, blood pressure, and respiratory rate increase by greater than 25% of the baseline values during the surgery, then children will receive an additional bolus of 1 μg/kg fentanyl.

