### Intraoperative anesthetic management and postoperative assessment

If the heart rate is reduced to less than 50 beats per min during the operation, then 10 μg/kg atropine will be used. If the blood pressure is reduced by greater than 25% of the baseline value, then 0.1 mg/kg ephedrine will be administered. At the end of surgery, sevoflurane will be discontinued, and the fresh gas flow will be increased to 6 l/min.

After completion of the operation, children will be transferred to the PACU and observed until the end of the study period. ECG results, noninvasive blood pressure, and pulse oximetry will also be measured every 5 min. After recovery of adequate of spontaneous breathing, purposeful movement, and eye opening, the endotracheal tube will be removed.

EA will be assessed using the PAED scale (Table 1) [24] at 0, 5, 10, 20, and 30 min after emergence from anesthesia. The PAED score will be documented by the same well-trained doctor, who will be blinded to the allocation group. The PAED score consists of five psychometric items: eye contact with the caregiver, purposeful action, awareness of surroundings, restlessness, and inconsolability. Each item is scored on a 5-point scale (0–4). The maximum score is 20. EA is defined as a PAED score greater than 10 points [25]. Patients with severe EA (PAED score ≥ 13) [24] will be treated with a bolus of 0.5 μg/kg fentanyl. The incidence of EA, frequency of severe EA, and duration of EA will be documented.

**Table 1 Tab1:** Pediatric Anesthesia Emergence Delirium (PAED) scale

1. The child makes eye contact with the caregiver	
2. The child’s actions are purposeful	
3. The child is aware of his/her surroundings	
4. The child is restless	
5. The child is inconsolable	

Items 1, 2, and 3 are reverse scored as follows: 4 = not at all, 3 = just a little, 2 = quite a bit, 1 = very much, 0 = extremely

Items 4 and 5 are scored as follows: 0 = not at all, 1 = just a little, 2 = quite a bit, 3 = very much, 4 = extremely

Scores for each item are summed to obtain a total PAED score between 0 and 20

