### Data collection and management

Clinical characteristics include age, gender, weight, body mass index (BMI), ASA grade, duration of surgery, and duration of anesthesia (from induction of anesthesia to the discontinuation of sevoflurane).

Intraoperative data collection will include the following parameters: heart rate, noninvasive blood pressure, respiratory rate, dose of sevoflurane, and collective fentanyl dose.

Postoperative data collection will include the PAED score at every time point, incidence of EA, frequency of severe EA, duration of EA, time of emergence (from discontinuation of sevoflurane to the first response to a simple verbal command), extubation time (from the end of anesthesia to extubation), CHEOPS score at every time point, the incidence of complications and adverse events, and the dose of fentanyl in PACU.

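### The between-arm safety outcome covers only postoperative (PACU) events, so procedural and intraoperative events that resolve earlier are left out, although the protocol plans to call the block safe

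*Protocol article*

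**What the plan says.** Four places in the protocol article fix the safety window, and they agree.

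- **Secondary objectives:** the groups are compared on postoperative complications.
- **Secondary outcomes:** the outcome is "The incidence of postoperative adverse events".
- **Intraoperative anesthetic management and postoperative assessment:** haemodynamic changes and complications are recorded in the PACU and compared between groups.
- **Data collection and management:** complications and adverse events are listed under postoperative data. The intraoperative list is "heart rate, noninvasive blood pressure, respiratory rate, dose of sevoflurane, and collective fentanyl dose".

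Other sections deal with what happens earlier. Under Randomization, the envelope is opened after intubation. The block-group section names one procedural risk ("To avoid a possible vascular puncture, repeated negative aspirations will be performed during all needle advancements"), requires at least 15 min between block and operation, and states "Immediate complications will be recorded and treated". The Control group section has no matching sentence. The shared management section gives rules for a low heart rate ("then 10 μg/kg atropine will be used") and for a fall in blood pressure ("then 0.1 mg/kg ephedrine will be administered").

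Both the Abstract and the main Discussion say that, if the hypothesis is confirmed, the block could be offered as a safe means of preventing emergence agitation.

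**The concern.** A randomized comparison of harms should start when the arms start to differ. Here they differ from shortly after intubation. One arm has a deep needle procedure and a local anesthetic injection; the other has an extra opioid bolus before incision. The safety outcome starts only after surgery. Harms that arise and resolve in between do not enter the named comparison, whichever arm they occur in.

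At stake is the safety half of the planned conclusion. The efficacy result does not depend on this point. A statement that a nerve block is safe does depend on what happened during the block and the operation, and the defined outcome does not cover that period.

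**Working it through.** No stated figure bears on this point, so there is none to reproduce. The check sets the sections against the order of events.

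| Period | What differs between arms | What is recorded | In the named safety comparison? |
|---|---|---|---|
| Envelope opening to incision | Block in one arm; fentanyl bolus before incision in the other | Block details by the anesthesiologist, sealed (Blinding); immediate complications (block-group text); monitored values every 5 min (Interventions) | No |
| Surgery | Effects of block or opioid; sevoflurane and fentanyl adjusted to response | Heart rate, blood pressure, respiratory rate, sevoflurane dose, total fentanyl dose, all patients | No |
| PACU | Persisting or new effects | Haemodynamic changes, complications, adverse events, both arms | Yes |

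**Step 1: is the window stated or merely omitted?** It is stated. The objective, the outcome, the data list and the assessment section all place complications after surgery.

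**Step 2: can the earlier events be recovered from other data?** In part. The variables that trigger the two rescue rules, heart rate and blood pressure, are collected during surgery in every child. If the 5-min recording also covers the interval between block and operation, that interval has at least 15 / 5 = 3 scheduled readings. Bradycardia and hypotension could be derived from such readings. The derivation would be incomplete: a value treated with atropine or ephedrine, or followed by a sevoflurane reduction, may have recovered by the next reading, and use of the two drugs is not on the list. No passage names the comparison. The Statistical analysis section gives only generic tests for continuous and categorical variables.

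**Step 3: are block-specific events captured?** They are provided for, through the sentence on immediate complications and the sealed block details. The envelope is opened only if medically necessary and at study completion, and no passage says how its contents join the safety outcome.

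**Step 4: what could be said from 50 children per arm?** This is context only, because the documents give no event rates. With 0 events in 50, the exact one-sided 95% upper bound is 1 − 0.05^(1/50) = 5.8% (two-sided 95%: 1 − 0.025^(1/50) = 7.1%). The chance of at least one event is 1 − (1 − p)^50. For assumed true rates p of 1%, 2% and 5% this is 39%, 64% and 92%. A safety statement from this trial is imprecise even with a full window, which is a further reason not to leave part of the window out.

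**The case against.** The strongest reply has four parts.

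1. **The data largely exist.** Heart rate and blood pressure are collected intraoperatively in both arms, and block details and immediate complications are recorded. This stands, and it rules out a reading that some will find tempting: that intraoperative harms can never be compared. What is missing is a named comparison and the rescue-drug use.

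2. **A strict like-for-like comparison is impossible for needle events.** This also stands. The control arm has no needle procedure ("Children assigned to the control group will receive a bolus injection of 1 μg/kg fentanyl intravenously before skin incision"), so vascular puncture can only be described in the block arm. It does not cover shared events such as hypotension and bradycardia.

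3. **The PACU window suits the blinding.** Staff there are blinded, and the comparison is recorded in both arms. As a comparison of postoperative events it is valid. It is simply narrower than the conclusion planned from it.

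4. **This is a condensed article.** A full case report form may list rescue drugs and intraoperative events. That is fair for the missing fields taken alone. It would not change the outcome and objective, which are worded as postoperative.

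Two further inferences should be resisted. A reader might conclude that complications are recorded only in the block arm. That rests on where one sentence sits; nothing says that control-arm events go unrecorded. A reader might also conclude that the late window favours the block. The documents give no timing or rate for any harm, and intraoperative effects of the control arm's extra fentanyl are left out too, so the net direction is unknown.

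**Conclusion.** The point holds in a limited form. The safety outcome begins after the period in which the block is given and surgery takes place, while the planned conclusion is about the safety of the block as such. Events that arise and resolve before the PACU are outside the between-arm outcome in both arms. Events that persist into the PACU, or first appear there, are inside it.

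Neither the size nor the direction of any distortion can be given. The conclusion rests on the article's own wording of the objective and outcome, and on the absence of any passage that brings intraoperative complications or rescue-drug use into a comparison. This is a secondary outcome: the emergence agitation analysis and the sample size are untouched. It should still be corrected, because a stated conclusion depends on it and the change is small.

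**What to change.** - In Secondary objectives, Secondary outcomes and Data collection and management, define the safety outcome as adverse events from randomization (envelope opening) onward.
- Use the same recording sentence in the block-group and control-group sections.
- Add intraoperative complications, atropine use and ephedrine use to the intraoperative data list.
- Compare shared events between arms: hypotension, bradycardia and rescue-drug use. Report needle- and local-anesthetic-related events descriptively for the block arm.
- Show intraoperative and postoperative events separately and combined.
- If this is not done, limit the safety statement in the Abstract and Discussion to the PACU period.

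The cost is wording in a few sections and a few added fields on the intraoperative record, with no extra patients and no change to treatment. There is one small downside: intraoperative items are recorded by the unblinded anesthesiologist, so they should be limited to objective events and drug use.

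Study time says the trial was completed in October 2018, whereas Trial status says it is still recruiting. If it has ended, the same definitions can be applied at analysis and reporting as far as existing records allow; where they do not, the narrower safety statement applies.
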